### Renal denervation procedure

The Recor Paradise System is a catheter-based system that delivers ultrasound energy to thermally ablate and disrupt the renal efferent and afferent sympathetic nerves, with the goal of achieving a reduction in systemic arterial BP and mitigating end-organ effects due to sympathetic over-activity. The system includes a single-use 6F catheter and an automated, portable, customized generator. The Paradise Catheter is intended to be employed in a catheterization laboratory under fluoroscopic guidance via femoral access only. The catheter consists of a through-lumen shaft with a cylindrical piezoelectric ceramic transducer located at the distal end of the catheter. The catheter has a distal balloon, which is pressurized by the generator to 1.5–2.0 atm using sterile circulating water.

The device's ultrasound transducer converts electrical energy into acoustic energy, which is then delivered radially through the cooling balloon into the renal artery. The pressurized balloon centers the ultrasound transducer within the artery, and the circulation of fluid serves as coolant to protect the endothelial and medial layers of the renal arterial wall. Each catheter has an embedded chip that communicates directly with the generator and specifies the power settings to be applied.

The uRDN procedure will be performed according to routine practice at each study site and consistent with the device’s instructions for use. As treatment is bilateral, specific angiographic requirements need to be met to deem anatomic eligibility. Measurements of the distal, mid, and proximal renal artery diameters are used to select the appropriate Paradise catheter balloon size. The treatment strategy requires operators to deliver a minimum of two (to three) sonications in each main renal artery and the first sonication should be delivered at a distance of at least 5 mm from the artery bifurcation. The Instructions for Use includes details for balloon sizing and treatment strategy regarding the number of emissions per artery and also includes instructions for additional sonications in case there are proximal bifurcations or accessory arteries. Physicians new to the technology will receive proctoring support for initial cases as needed.

Procedural support by a sponsor representative is available to all sites regardless of experience with the Paradise Renal Denervation System.

### Assessments and data collection

Follow-up visits are scheduled at 3, 6, and 12 months after the uRDN procedure and every 12 months thereafter. Each visit will include medical review, measurement of office BP, medication name and dose). Ambulatory BP data (mean values, heart rate, standard deviation) obtained during routine clinical practice at study centers (including daytime, nighttime and 24-h BP) will be recorded and assigned to the nearest follow-up visit.

Other data collected during routine clinical practice will also be reviewed as part of patient follow-up, including any of the following: physical parameters including body weight, HR, seated and standing office BP; smoking status during follow-up, socioeconomic, and healthcare resource use parameters; electrocardiogram; non-invasive cardiac imaging; urinalysis including micro/macroalbuminuria; blood chemistry (serum creatinine, electrolytes, blood glucose and HbA1c, blood lipids); non-invasive renal artery imaging; any other cardiovascular procedures and treatments including glucose- and cholesterol-lowering drugs and antiplatelet/anticoagulant use, and the occurrence of any cardiovascular/cerebrovascular event (MI, HF, AF, etc.) and cardiovascular or non-cardiovascular death.

### Home blood pressure

All clinical sites will be provided with validated, commercially available, validated telemetric home BP monitoring (HBPM) devices BPM Connect Pro, WITHING, Issy-les-Moulineaux, France) [19]. The collection of home blood pressure with this WITHING device is specific to the execution of the study and is not currently part of the sites' routine clinical practice. Prospectively enrolled subjects who elect to be part of HBPM data collection will be provided with a device and will be instructed to record their home BP according to the American Heart Association and American Medical Assocation [20] for seven consecutive days prior to the uRDN procedure. Over this period, subjects will take two measurements in the morning and two measurements in the evening. Consistent with current recommendations [20, 21], patients will be instructed to avoid smoking, caffeinated beverages, or exercise in the 30 min prior to home BP measurement, to take readings in a quiet room after sitting quietly for 5 min, to sit with their back straight and supported and feet flat on the floor with the arm supported on a flat surface and the upper arm at heart level. The same arm with the highest BP determined previously will be used for all home BP measurements, and at least two measurements should be taken 1–2 min apart before taking medications in the morning, and before taking medications and before dinner in the evening. All home BP measurements will be transmitted automatically via cellular or wifi signal by the HBPM device to a dedicated secured cloud-based platform (Study Pal; DELVE; www.delvehealth.com), which is GDPR 2016/679 compliant. The use of this integrated Global System for Mobile communication functionality removes the need and burden for participants to record home BP measurements in a diary.

Subjects will be reminded by automatic text message to measure their home BP if their home BP assessment is incomplete. Ideally seven- but a minimum of 3-day HBPM data (at least twelve valid measurements) are recommended prior to the procedure. Patients participating in home BP data collection will measure their home BP every 3 months during follow-up, ideally over 7 days of measurements with four readings per day prior each visit at the study site. If insufficient baseline home BP data are collected, no additional home BP data will be collected for that patient. Subjects who are unwilling and/or unable to comply with HBPM requirements will not take part in HBPM data collection but will continue to be part of the registry. Retrospectively enrolled subjects will not be provided with a HBPM device, and any available BP data (office, HBP, ABPM) from prior to the uRDN procedure will be collected retrospectively.

### Patient-reported outcomes

The validated Short Form (SF)-12 questionnaire is a 12-item questionnaire that gathers data on patient functional health and well-being. The patient may elect to complete the SF-12 quality-of-life questionnaire as part of the study specific assessments. If patients agree to complete the questionnaire, they will be asked to complete the questionnaire in their local language at enrollment, at 3, 6, and 12 months after the uRDN procedure, and annually thereafter.

### Safety

All centers participating in the GPS Registry will use the Paradise uRDN system per their normal practice. Therefore, any device-related adverse events will be reported to the appropriate regulatory authorities through the Recor Medical vigilance reporting process. Underlying diseases/pre-existing conditions will not be reported as adverse events unless there has been a substantial increase in the severity or frequency of the problem that cannot be attributed to natural history during the course of the registry. The assessment of safety includes but is not limited to collecting the following events: incidence of new onset end-stage renal disease (eGFR < 15 mL/min/m^2^ or need for renal replacement therapy), significant decline in renal function, new renal artery stenosis > 70% by CTA/MRA, incidence of renal artery perforation or dissection requiring intervention, incidence of hospitalizations for hypertensive crisis or symptomatic hypotension.

### Data collection and storage

Subject data will be collected into an electronic data capture system. The data will be monitored and audited for data collection to assess continued compliance with the protocol and applicable regulations to ensure the integrity of the data. Data processing will be performed in compliance with the European Union General Data Protection Regulation (GDPR) 2016/679, and all applicable national laws to ensure data governance policies and guidelines, including data ownership, data access, data sharing, and data use agreements are managed properly.

### Sample size

The sample size for the Registry is based on the intent to characterize the safety and effectiveness data in a real-world patient population. The target is to enroll up to 3000 patients at up to 200 sites globally and follow them up to 5 years after enrollment. This sample size should provide a high degree of statistical precision on home and office blood pressure changes and a high probability of observing rare safety events; with a sample size of 3000 subjects, there is a 95% probability of observing events that occur at a population rate as low as 0.1%.

### Statistical analysis

Every effort will be made to minimize the amount of missing data. Statistical analyses will be descriptive. Continuous variables will be summarized as mean ± standard deviations and median (range) with interquartile range. Categorical variables will be summarized as frequencies and percentages. Analysis of clinical effectiveness and safety (Table 2) data will be performed on the total study population and in clinically relevant participant subgroups (e.g., based on age, history of chronic kidney disease, heart failure, atrial fibrillation, sleep apnea, diabetes mellitus, etc.). An additional analysis will determine whether BP parameters can help predict patients that may be more likely to respond to uRDN. Subgroup analyses and multivariable analyses will be performed.

**Table 2 Tab2:** Standard of care parameters collected, effectiveness and safety assessments

Standard of care parameters
Demographics
Medical history
Office blood pressure
Medication usage
Short Form-12 quality-of-life questionnaire
Socioeconomic and healthcare resource use parameters
24-h ambulatory blood pressure monitoring
Electrocardiogram
Cardiac imaging
Urine chemistry
Blood chemistry
Renal artery imaging
Renal denervation procedure
Cardiovascular procedures and treatments

Effectiveness assessments
Reduction in average home systolic/diastolic BP in mmHg compared with enrollment
Reduction in average office systolic/diastolic BP in mmHg compared with enrollment
Reduction in average ambulatory systolic/diastolic BP in mmHg (daytime, nighttime and 24-h) compared with enrollment
Proportion of patients with home, office and ambulatory systolic BP reductions of ≥ 5 mmHg, ≥ 10 mmHg, and ≥ 15 mmHg post procedure
Proportion of patients meeting BP control criteria at follow-up (according to current guidelines)
Change in office/home/ambulatory pulse pressure in mmHg at follow-up compared with enrollment
Change in office/home/ambulatory heart rate in beats/min at follow-up compared with enrollment
Proportion of subjects without any antihypertensive treatment at follow-up, with analysis stratified by number of antihypertensive medications at enrollment
Analysis of quarterly home BP in mmHg at follow-up
Change in Short Form-12 quality-of-life scores during follow-up compared with enrollment

Safety assessments
All-cause mortality
Hospitalization for major cardiovascular- or hemodynamic-related events (e.g., heart failure, atrial fibrillation)
Hypertensive crisis or symptomatic hypotension
New-onset stroke, transient ischemic attack, cerebrovascular accident
Acute myocardial infraction
Any coronary revascularization
Major vascular complication (e.g., clinically significant groin hematoma, arteriovenous fistula, pseudoaneurysm) requiring surgical repair, interventional procedure, thrombin injection, or blood transfusion)
New renal artery stenosis > 70% confirmed by CTA/MRA
Renal artery perforation or dissection requiring an invasive intervention
New-onset (acute) end-stage renal disease (eGFR < 15 mL/min/m^2^ or need for renal replacement therapy)
Significant decline in renal function, defined as a ≥ 50% increase in serum creatinine (mg/mL)

BP, blood pressure; CTA, computed tomography angiography; eGFR, estimated glomerular filtration rate; MRA, magnetic resonance angiography

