**Methods:**

The study aims to enroll up to 3000 patients undergoing uRDN in routine clinical practice. Patients will be recruited over a 4-year period and followed for 5 years (at 3, 6, and 12 months after the uRDN procedure and annually thereafter). Standardized home BP measurements will be taken every 3 months with automatic upload to the cloud. Office and ambulatory BP and adverse events will be collected as per routine clinical practice. Quality-of-Life questionnaires will be used to capture patient-reported outcomes.

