Ambulatory, home, and office BP measurements provide complementary information [25]. While ambulatory and office BP measurements were used in most of the randomized clinical trials and registries, limited information on the impact of RDN on home BP at long-term follow-up is currently available. The GPS Registry will provide the unique opportunity to assess teletransmitted home BP every 3 months with a dedicated telemetric device. Out-of-office home BP measurements are more reproducible than office measurements and are more closely associated with hypertension mediated organ damage (HMOD) and the risk of cardiovascular events and are thus recommended by several hypertension management guidelines [6, 8, 20]. Furthermore, the use of HBPM will facilitate increased data collection in patients over time to see how their BP evolves following uRDN. It will also permit ongoing data collection in the GPS Registry even in the event of further outbreaks of the COVID-19 or other pandemic [29]. As has been shown, one of the biggest limitations of a registry is losing subjects to follow-up. A benefit of collecting home BP is that the data will be automatically uploaded to the cloud, which will enable better long-term follow-up of patients regardless of attendance for office visits and it will allow for the collection of BP between the visits.

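### Frequencies and percentages are the only summary named for safety events that accrue over five years; once patients are lost, either obvious crude percentage misstates the 5-year risk

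*Protocol article*

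**What the plan says.** The Statistical analysis section of the protocol article states that "Statistical analyses will be descriptive" and that "Categorical variables will be summarized as frequencies and percentages". It then says that analysis of effectiveness and safety "data will be performed on the total study population and in clinically relevant participant subgroups". It adds that "Subgroup analyses and multivariable analyses will be performed", without naming a model. It mentions no censoring, person-time or cumulative-incidence method, and gives no denominator for event percentages at a given time.

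The safety list in Table 2 mixes two kinds of event. Some can occur at any time over follow-up, starting with "All-cause mortality" and including stroke, myocardial infarction, coronary revascularization, hospitalization, renal artery stenosis, end-stage renal disease and decline in renal function. Others, such as groin complications and renal artery perforation or dissection, are essentially procedural.

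On follow-up, the Abstract says "Patients will be recruited over a 4-year period and followed for 5 years". The Sample size section says "The target is to enroll up to 3000 patients at up to 200 sites globally and follow them up to 5 years after enrollment", and Study design calls the five years recommended. The Discussion remarks that "one of the biggest limitations of a registry is losing subjects to follow-up".

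**The concern.** Whether a patient has died or had a stroke is a categorical variable, so the one stated summary, read together with the stated population, most naturally gives events divided by all enrolled. That percentage treats a patient lost at month 6 as if observed event-free for five years. The result then depends on retention as well as on the true risk.

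Long-term safety is a leading aim of the registry, and the Discussion presents registries as support for long-term safety claims. Loss also need not be equal across groups. If retention differs between, say, patients with and without chronic kidney disease, crude subgroup percentages would differ even where the risks are equal.

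The article's answer to loss to follow-up is automatic upload of home blood pressure. That protects blood pressure data. It does not by itself capture deaths or hospitalizations, and retrospectively enrolled patients are not given the device.

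**Working it through.** **Inputs from the article.** Up to 3000 patients, 4 years of accrual, 5 years of follow-up per patient. No loss rate and no long-term event rate are given.

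**Assumed.** Constant event hazard, independent constant loss, and 10%, 20%, 30% or 50% of patients lost by year 5.

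**1. The article's own figure.** The Sample size section gives a 95% probability of observing an event with a population rate of 0.1%. Check: 1 − (1 − 0.001)^3000 = 0.9503. It reproduces and is not in dispute here.

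**2. Crude percentage of all enrolled.** Let R be the true 5-year risk and L the share lost by year 5. Then λ = −ln(1 − R)/5 and μ = −ln(1 − L)/5, and

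crude = λ/(λ + μ) × [1 − exp(−5(λ + μ))].

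Example with R = 10%, L = 30%: λ = 0.0211, μ = 0.0713, λ/(λ + μ) = 0.228, exp(−5(λ + μ)) = 0.9 × 0.7 = 0.63. So crude = 0.228 × 0.37 = 0.0844.

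**3. The other crude denominator.** Count only patients with an observed event or seen event-free at year 5. The latter share is (1 − R)(1 − L), so the percentage is crude/[crude + (1 − R)(1 − L)]. In the example, 0.0844/(0.0844 + 0.63) = 11.8%.

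**4. Results for a true 5-year risk of 10%.**

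| Lost by year 5 | Events / all enrolled | Ratio to truth | Events / (event or event-free at year 5) |
|---|---|---|---|
| 10% | 9.5% | 0.95 | 0.0950/(0.0950 + 0.81) = 10.5% |
| 20% | 9.0% | 0.90 | 0.0898/(0.0898 + 0.72) = 11.1% |
| 30% | 8.4% | 0.84 | 0.0844/(0.0844 + 0.63) = 11.8% |
| 50% | 7.3% | 0.73 | 0.0726/(0.0726 + 0.45) = 13.9% |

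The ratio in the third column hardly depends on the true risk. From R = 0.1% to R = 20% it runs from 0.949 to 0.951 at 10% loss, and from 0.721 to 0.731 at 50% loss.

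**5. The same on an annual scale.** Loss of 10% per year is 1 − 0.9^5 = 41% by year 5. A true 5% is then reported as 3.90% and a true 10% as 7.81%, a ratio of 0.78.

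**6. Staggered entry alone.** Take uniform accrual over 4 years, no loss, and R = 10%. At 9 years after first enrollment everyone has five years and the ratio is 1.00. If data were cut at 8, 7, 6 or 5 years, the ratio would be 0.98, 0.90, 0.78 or 0.61.

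**7. Procedural events.** With 30% lost by year 5, the share still followed at day 30 is exp(−0.0713 × 30/365.25) = 0.994. Plain percentages are adequate there.

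**The case against.** The strongest reply is that the quoted sentence is a general rule, the counterpart of the one on continuous variables. It names no safety outcome, no horizon and no denominator. Kaplan-Meier curves and incidence rates are themselves descriptive, so nothing in the article excludes them, and a journal article commonly leaves censoring rules and estimators to an analysis plan. This stands to the extent that the article cannot be said to have ruled out a better method. It does not dispose of the point, because the article does name a summary for such data and a population, and that summary followed as written is biased under loss.

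Several stronger readings are tempting and are not supported:

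- A reader might infer that understatement is certain. It is not: the denominator is not given, and the second crude choice errs upward.
- A reader might infer that the 4-year accrual biases the 5-year results. With five years planned for each patient it does not, and the article describes no earlier data cut.
- A reader might take the Discussion to predict heavy loss in this registry. It speaks of registries in general, calls loss one of the biggest limitations rather than the main one, and presents home monitoring as a way to improve follow-up.
- A reader might apply the point to every event in Table 2. The procedural ones are essentially untouched.

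**Conclusion.** The point holds in a limited form. For safety events that accrue over follow-up, the only summary the article names does not estimate 5-year risk without bias unless follow-up is complete, and the article itself recognizes loss to follow-up as a problem for registries. On the natural reading (all enrolled as denominator), the reported risk would be about 5% to 27% too low in relative terms for 10% to 50% loss by year 5. On the alternative denominator it would be too high.

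These sizes are illustrative. They rest on assumed loss rates, constant hazards and loss that is independent of risk; the documents supply none of these. The direction for each denominator follows from the censoring, but which denominator will be used is not stated.

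**What to change.** State in the analysis section that long-term safety events are measured from the procedure and censored at last contact. Use Kaplan-Meier for all-cause mortality and cumulative incidence with death as a competing event for non-fatal outcomes. Report each with a 95% confidence interval and numbers at risk, for example at 1, 3 and 5 years. Keep plain percentages for peri-procedural events. If the analysis plan already specifies this, a sentence confirming it is sufficient.

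The sponsor should also confirm that event dates and last-contact dates are recorded, since the article does not say so and the method depends on them.

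The cost is modest programming and stated risks slightly less favourable than percentages of all enrolled. No patient procedure changes. These estimators still assume that loss is unrelated to risk, so the number lost and the completeness of follow-up should be reported beside them.

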### Study population

Based on the international guidelines that have been recently published, patients qualifying for renal denervation should have been unsuccessful in controlling their blood pressure with lifestyle changes and antihypertensive medications. Patients selected for uRDN with the Paradise System as per routine clinical practice on patient selection for renal denervation can be enrolled in the registry. The goal of the study is to collect real-world data on current clinical practices at each participating site. Full details of the study inclusion and exclusion criteria are shown in Table 1. For prospectively enrolled patients, the uRDN procedure is to be scheduled within 30 days of registry enrollment, while retrospectively enrolled patients need to have undergone uRDN within the previous 6 months.

**Table 1 Tab1:** Inclusion and exclusion criteria

Inclusion criteria
Age ≥ 18 years at time of consent
Candidate for uRDN with the Paradise System based on physician’s assessment
OR
Treated with uRDN using the Paradise System within the 6 months prior to consent
Willing to provide written informed consent (appropriately signed and dated) and agreed to have all study procedures performed

Exclusion criteria
Stented renal artery
Age < 18 years
Pregnancy
Known allergy to contrast medium not amenable to treatment
Renal arteries with diameter < 3 mm and > 8 mm^a^
Renal artery with fibromuscular disease^a^
Renal artery aneurysm or dissection^a^
Renal artery stenosis of any origin > 30%^a^
Iliac/femoral artery stenosis precluding insertion of the Paradise catheter^a^

^a^Determined at time of procedure

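### Table 2 measures change from enrollment, which falls after treatment for retrospective patients: unavoidable for SF-12, and at odds with the planned collection of pre-procedure readings for blood pressure

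*Protocol article*

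**What the plan says.** Seven of the ten effectiveness lines in Table 2 of the protocol article name enrollment as the reference. They are the changes in home, office and ambulatory blood pressure (BP), pulse pressure, heart rate and SF-12, and the stratifier of the off-medication outcome. Typical wordings are "Reduction in average office systolic/diastolic BP in mmHg compared with enrollment", "Reduction in average home systolic/diastolic BP in mmHg compared with enrollment", "Change in Short Form-12 quality-of-life scores during follow-up compared with enrollment" and, for the stratifier, "with analysis stratified by number of antihypertensive medications at enrollment". The responder line does not name enrollment. It reads "systolic BP reductions of ≥ 5 mmHg, ≥ 10 mmHg, and ≥ 15 mmHg post procedure".

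Enrollment has two meanings under Study population. Prospective patients enrol first and have the procedure scheduled within 30 days. By contrast, "retrospectively enrolled patients need to have undergone uRDN within the previous 6 months".

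Two other sections bear on what a retrospective patient can contribute:
- Home blood pressure: these patients receive no study device, but "any available BP data (office, HBP, ABPM) from prior to the uRDN procedure will be collected retrospectively".
- Patient-reported outcomes: of patients who agree to the SF-12, "they will be asked to complete the questionnaire in their local language at enrollment", with later questionnaires at 3, 6 and 12 months after the procedure and then yearly.

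The Statistical analysis section applies the effectiveness analysis to the whole registry population and to clinical subgroups.

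**The concern.** The same word marks a point before treatment in one group and after treatment in the other, and the two groups are pooled. A change from a post-treatment reference leaves out whatever effect came before it. If Table 2 is followed literally, a pooled mean change mixes two different quantities, and its value depends partly on how many patients happened to enrol retrospectively.

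The stratifier has a similar problem. A patient whose drugs were reduced between procedure and enrollment would be classified by the reduced count, so part of the outcome would be built into the stratum.

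The article justifies its sample size partly by precision on home and office BP change. A larger sample does not reduce an error of this kind.

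**Working it through.** **The plan's own figure.** The only design figure is a 95% chance of seeing an event with a true rate of 0.1% in 3000 patients. It reproduces: 1 − (1 − 0.001)^3000 = 0.9503. The present point does not depend on it.

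**Timing.** Prospective enrollment comes before the procedure, within 30 days. Retrospective enrollment comes 0 to 6 months after it. Follow-up visits are timed from the procedure (Assessments and data collection). For someone who enrols at month 5, the 3-month visit comes before enrollment, so a change from enrollment to that visit would place the follow-up value ahead of its reference. The literal rule cannot work for such a patient.

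**SF-12.** The first questionnaire is at enrollment. A retrospective patient is already treated by then, so every change score compares one post-procedure value with another. No size or direction can be computed, because the article gives no SF-12 effect.

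**Office and ambulatory BP.** Let:
- D = true fall from before to after the procedure. For illustration, the Discussion cites an observational European study with 12-month systolic falls of 15 mmHg (office) and 7.5 mmHg (24-hour ambulatory).
- f = share of patients in the change analysis who enrolled retrospectively. Not stated; assumed.
- g = share of the fall already present when they enrol. Not stated; assumed 50% to 100%.

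With enrollment as the reference for everyone:

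pooled fall = (1 − f)·D + f·D·(1 − g) = D − f·g·D

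The understatement is therefore f·g·D.

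| D (mmHg) | f | Loss, g = 50% | Loss, g = 100% | Pooled fall |
|---|---|---|---|---|
| 15 (office) | 10% | 0.10 × 0.5 × 15 = 0.75 | 0.10 × 1 × 15 = 1.5 | 14.25 to 13.5 |
| 15 (office) | 25% | 0.25 × 0.5 × 15 = 1.9 | 0.25 × 1 × 15 = 3.75 | 13.1 to 11.25 |
| 7.5 (24-hour) | 10% | 0.10 × 0.5 × 7.5 = 0.4 | 0.10 × 1 × 7.5 = 0.75 | 7.1 to 6.75 |
| 7.5 (24-hour) | 25% | 0.25 × 0.5 × 7.5 = 0.9 | 0.25 × 1 × 7.5 = 1.9 | 6.6 to 5.6 |

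If the pre-procedure value is the reference, g = 0 and the loss is zero for any f.

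**Home BP.** Retrospective patients get no device, so the quarterly transmitted series comes from prospective patients, whose readings start in the week before the procedure. This outcome is little exposed.

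**The case against.** The strongest reply is that pre-procedure BP is collected for retrospective patients, and it is hard to see a purpose for that other than a baseline. The Home blood pressure section also uses the word baseline for readings taken before the procedure. On this view, enrollment in Table 2 is loose wording for the baseline record, and the full protocol or analysis plan, not shown here, may say so.

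Much of this stands for BP. A reader might infer that the pooled BP results are wrong. The documents do not support that: they show a conflict between two sections and an attenuation that arises only if Table 2 is applied as written. A reader might also infer that every effectiveness outcome is affected. It is not: the responder line says only that reductions are post procedure, and BP control and quarterly home BP are follow-up values. Nor is a large loss established. A 50% retrospective share with the whole fall already present would give 0.50 × 1 × 15 = 7.5 mmHg, but nothing in the article supports either assumption. The analyses are descriptive, with no hypothesis test that could be invalidated.

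The reply does not dispose of the point. Table 2 states a reference, so this is not a detail merely left to another document, and the stated reference does not fit the article's own enrollment rule. Pre-procedure BP is promised only where available, so some patients may have none, and under the present wording their enrollment value would stand in. For SF-12 there is no pre-procedure value to fall back on.

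**Conclusion.** The point holds as a wrongly fixed reference.
- **SF-12:** the defect is firm for retrospective patients who complete the questionnaire. Its size is unknown.
- **Office and ambulatory BP:** Table 2 and the Home blood pressure section need to be reconciled. Read literally, the office fall is understated by 0.75 to 1.5 mmHg at f = 10% and by 1.9 to 3.75 mmHg at f = 25%. This rests on an illustrative D of 15 mmHg and on assumed f and g. It is zero wherever the pre-procedure value is used.
- **Pulse pressure, heart rate and medication stratifier:** the same wording problem applies. No size can be given.
- **Home BP:** little affected.

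**What to change.** In the seven Table 2 lines that name enrollment, define baseline as the value before the procedure. For home BP this should be the pre-procedure multi-day average, since a single last reading would not match the 7-day scheme (minimum 3 days and twelve valid measurements). For the stratifier, use the number of antihypertensive drugs before the procedure, where recorded. State the same baseline for the responder proportions.

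Exclude from each change analysis the patients without a pre-procedure value, and report how many there are. Restrict SF-12 change to patients with a pre-procedure score, which in practice means those enrolled prospectively.

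The cost is a wording change in Table 2 and in the analysis plan, plus the loss of an unknown number of retrospective patients from the change analyses. For BP the change relies on data the article already plans to collect. Whether pre-procedure drug counts are on record for all retrospective patients cannot be judged from the article.
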